## Abstract

Background: Secondary hydrocephalus is a well-known complication of severe acquired brain injuries (sABIs) often diagnosed during inpatient rehabilitation. Currently, there is no gold standard for its detection. Therefore, we designed a novel clinical diagnostic protocol that integrates clinical, functional, biochemical and neuroradiological assessments to improve the accuracy of its diagnosis in patients with sABIs. Methods: This prospective cohort study will be conducted in a tertiary referral rehabilitation center in Italy. A historical cohort of patients will be compared with a prospective cohort undergoing the new clinical diagnostic protocol. Expected Results: The expected results include an increase in the proportion of diagnosed cases, a reduced incidence of clinical complications, an increase in the rehabilitative outcomes at discharge, a significant reduction in the length of hospital stay, and useful information about the diagnostic and prognostic value of the neuroradiological characteristics. Conclusion: We expect that this clinical diagnostic protocol will result in a more appropriate assessment and timely treatment of secondary hydrocephalus in patients with sABIs, with the ultimate goal of improving their prognosis. In addition, it could be adopted by other rehabilitation centers to improve hydrocephalus diagnosis and treatment, thereby reducing the length of hospital stay and accelerating recovery with benefits for both patients and hospitals.

## 1. Introduction

Secondary hydrocephalus is a pathological condition caused by the accumulation of cerebrospinal fluid (CSF), probably as a consequence of damage in its reabsorption mechanisms. It is a well-known complication of severe acquired brain injuries (sABIs), often diagnosed during inpatient rehabilitation [1,2,3]. The incidence of chronic secondary hydrocephalus is reported to range between 14 and 45%, and it is usually diagnosed between 3 and 12 months after brain injury [1,4,5,6,7].

Detecting secondary hydrocephalus in patients with sABIs is complex, due to their neurological impairment, difficulties in autonomously reporting symptoms and the actual lack of standardized methods of diagnosis. Moreover, even when a clear ventriculomegaly is found on CT or RMN scans, it is sometimes difficult to understand whether it is secondary to brain atrophy or the accumulation of CSF [1,2,5]. Hydrocephalus in patients with sABIs can present either with symptoms related to chronic hydrocephalus (cognitive impairment, gait disturbances and urinary incontinence) or with features more related to increased intracranial pressure (headache, papilledema, nausea, vomit and worsening of consciousness) [5,8]. In the absence of a gold standard for the diagnosis of secondary hydrocephalus, its recognition is often based on the combination of clinical observation and radiological findings. Subarachnoid and/or intraventricular hemorrhage, decompressive craniectomy, duration of coma, severity of brain injury (measured using the Glasgow Coma Scale score) and older age are reported as the main risk factors for hydrocephalus [4,6,9,10]. The main diagnostic criteria include a persistent disorder of consciousness, worsened or plateaued clinical recovery, elevated CSF pressure and/or clinical improvement in behavioral or motor capacities after high-volume lumbar puncture [3,11,12].

Given the difficulties in its diagnosis and treatment, the identification of hydrocephalus is important to clinicians dealing with the rehabilitation of patients with sABIs because it may delay or negatively affect their recovery. Moreover, being a treatable condition, early diagnosis and correct management are fundamental to identify patients who may be selected for surgical treatment, which is associated with a better outcome [2,4,6,10,11,13,14,15,16]. Surgical treatment usually consists in the placement of a ventriculoperitoneal shunt (VPS) or ventriculoatrial shunt (VAS) [13,14,15].

In a previous study, a 13.2% incidence of secondary hydrocephalus was reported among 621 hospitalized patients with sABIs [7]. The diagnosis was based on the previously indicated combination of clinical and radiological criteria, but we hypothesized that cases may have been under-detected, especially in patients with disorders of consciousness and/or many confounding comorbidities, due to the absence of a reference standard. In addition, the study showed that after VPS placement, most patients had a clinical improvement and none worsened; however, a delay in surgical treatment resulted in a longer hospitalization and was associated with worse outcomes. That study underscored the need for a more standardized approach to the diagnosis of secondary hydrocephalus, with a better timing in the evaluation of patients with sABIs during inpatient rehabilitation in order to improve the selection of those who may benefit most from surgical treatment [17].

In this position paper, we describe a diagnostic protocol for hydrocephalus that integrates clinical, functional, biochemical and neuroradiological assessments. The aims of the protocol are as follows:To increase the hydrocephalus detection rate;To reduce the time for hydrocephalus diagnosis/surgical treatment;To improve the clinical rehabilitative outcomes at discharge;To reduce the overall length of hospitalization (LOS) and the occurrence of complications in patients diagnosed with and treated for hydrocephalus.

## 2. Materials and Methods

### 2.1. Study Design, Setting and Population

The protocol will be applied to a prospective cohort recruited in a tertiary referral rehabilitation center in Italy, highly specialized in sABIs. Patients aged 18 or older with a diagnosis of an sABI of any etiology will be eligible for the study. Exclusion criteria are as follows: diagnosis and/or treatment of hydrocephalus prior to hospital admission at our institution; presence of acute hydrocephalus; pre-existing neurological or psychiatric comorbidities. 

Patients with and without a diagnosis of hydrocephalus in this prospective cohort will be compared in terms of clinical rehabilitative outcomes, the evolution of quality of life and neuroradiological characteristics.

A historical cohort will serve as a control group and will include all hospitalized patients with sABIs between 1 January 2015 and 31 December 2019. The years 2020 and 2021 will be excluded in order to avoid selection bias due to the organizational measures taken to counteract the impact of the SARS-CoV-2 pandemic. 

### 2.2. Feasibility 

Patients with sABIs of different etiologies (traumatic, vascular, anoxic, infectious, neoplastic, etc.) will be recruited from those hospitalized in the Severe Acquired Brain Injury Unit or in the Intensive Care Unit (ICU), depending on their clinical conditions. The presence of an ICU in our rehabilitation institute ensures prompt treatment soon after the acute brain injury event, through the implementation of a personalized rehabilitation project in the early stage.

The recruitment of the prospective cohort will last two years. The expected annual flow of patients with sABIs is 50–60, and the expected proportion with hydrocephalus is about 20%, leading to a total number of 100–120 patients with sABIs and at least 20 patients with a confirmed diagnosis of hydrocephalus.

### 2.3. Ethics 

The study protocol has been approved by the local ethics committee (CE-AVEC N° 191-2022-OSS-AUSLIM; 17 March 2022), and the study did not receive funding. All participants will sign an informed consent form to participate in the study. In case of an inability to give consent, this will be acquired from the caregiver according to article 4 of Law n. 219, 22 December 2017. In the historical cohort, informed consent will be obtained whenever possible; otherwise, it will be waived in accordance with the General Authorization of the Privacy Guarantor No. 09/2016 for observational retrospective studies.

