### 2.5. Statistical Analysis Plan

Continuous variables will be presented as the mean and standard deviation or as the median and interquartile range. Normality in the distribution will be tested with the Shapiro–Wilk test. Categorical variables will be summarized in terms of absolute and relative frequencies.

To determine whether the new diagnostic protocol can improve the ability to detect hydrocephalus as well as the timeliness of the diagnosis and the clinical rehabilitative outcomes, the historical and prospective cohorts will be compared with respect to the following: hydrocephalus diagnosis detection rate, time from admission to diagnosis, LOS, incidence of clinical complications, and DRS and LCF scores at discharge (T3). In the subgroup of patients with low responsiveness, the clinical rehabilitative outcome at discharge will be measured using the CRS-R score. Continuous variables will be compared using Student’s *t* test, when normally distributed, or the Mann–Whitney U test otherwise. Categorical variables will be compared using Pearson’s χ^2^ test or Fisher’s exact test as appropriate. The same tests will be used to compare patients with and patients without a diagnosis of hydrocephalus belonging to the prospective cohort, in terms of the following: clinical rehabilitative outcome at T3 and T4 measured using the DRS, LCF and CRS-R scale scores; evolution from T0 to T4 of quality of life measured using the QOLIBRI-OS; neuroradiological characteristics at T1 and T3 or T4 measured using Evan’s index, callosal angle and volumetric analysis. To complement the information provided by the statistical tests, differences between groups will be quantified in terms of the effect size (standardized mean differences for continuous variables; difference between proportions or odds ratios for categorical variables) and its standard error. In addition, outcome variables will be compared between the historical and prospective cohorts, adjusting for demographic and clinical confounders in multivariable regression analyses. Confounders to be included in the models are those significantly associated with the outcomes and significantly different between the two cohorts. 

Two-sided tests will be carried out, and the statistical significance level will be set at 0.05. All analyses will be performed with Stata version 17.0 (Stata Corp., College Station, TX, USA).

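### Prospective patients enter only at consent, historical patients at admission: a risk that very early exits are counted in one cohort and not in the other

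*Protocol article*

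**What the plan says.** The Protocol article sets the entry rules in two places.

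- **Prospective cohort, section 2.3:** "All participants will sign an informed consent form to participate in the study". For patients who cannot decide for themselves: "In case of an inability to give consent, this will be acquired from the caregiver". No waiver is mentioned for this cohort.
- **Historical cohort, section 2.1:** the control group "will include all hospitalized patients with sABIs between 1 January 2015 and 31 December 2019".
- **Historical cohort, section 2.3:** "In the historical cohort, informed consent will be obtained whenever possible; otherwise, it will be waived".

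Section 2.5 then compares the two cohorts on "hydrocephalus diagnosis detection rate, time from admission to diagnosis, LOS, incidence of clinical complications, and DRS and LCF scores at discharge (T3"). The only allowance for differences between cohorts is regression on measured covariates: "Confounders to be included in the models are those significantly associated with the outcomes and significantly different between the two cohorts".

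The article does not say when prospective consent is taken or what happens to a historical patient who is reached and declines. It gives no rates of early death, transfer, refusal or failed contact. The limitations in the Discussion are that randomisation is not feasible and that historical data may be incomplete; selection through consent is not among them.

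**The concern.** The two cohorts start at different points. A historical patient is counted from admission, because the waiver keeps in anyone who can no longer be asked, including those who died. A prospective patient is counted only once consent exists. Whoever dies or is transferred in between is absent from the prospective denominator, but the matching patient of 2015–2019 is present in the historical one.

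Such patients have almost no chance of being diagnosed. In section 2.4 the second imaging round comes at about 30 days and the first team meeting at about 40 days. Keeping them in one cohort only would lower the historical detection rate and so overstate the gain from the new protocol. Their short stays would lower historical LOS and so hide part of any reduction. Time from admission to diagnosis is not affected by this route if it is computed among diagnosed patients.

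Applying the same exclusion criteria to both cohorts would not cure this, because the cause is the start of counting and not eligibility. Nor would covariate adjustment, which cannot supply patients who were never enrolled.

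**Working it through.** **1. The plan's own figures.** Section 2.2 gives 50–60 patients a year, and "The recruitment of the prospective cohort will last two years". 2 × 50 = 100 and 2 × 60 = 120 patients; at 20% with hydrocephalus, 20 and 24 cases. These reproduce the stated 100–120 and at least 20. They equal the whole expected flow, so they make no visible allowance for patients lost before consent.

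**2. The entry rules side by side.**

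| Patient | Prospective | Historical |
|---|---|---|
| Dies or is transferred before consent could be taken | Not counted | Counted, under the waiver |
| Cannot consent for lack of capacity | Counted, with caregiver consent | Counted |
| Asked and refuses | Not counted | Not stated |

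The first row differs on the rules as written. The third may differ, but the documents do not settle it.

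**3. Effect of early exits on the detection rate (illustrative).** Let e be the share of historical admissions that leave before a prospective patient could have been consented, none of them diagnosed. The documents do not give e; 3–10% is assumed. The Introduction's 13.2% from an earlier study of 621 patients stands in for the recorded historical rate. The rate among patients comparable with the prospective cohort is 0.132/(1 − e). The last column uses the gap to the expected 20%, which is 20 − 13.2 = 6.8 points.

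| e | Comparable rate | Shift (points) | Share of the 6.8-point gap |
|---|---|---|---|
| 3% | 13.6% | 0.4 | 6% |
| 5% | 13.9% | 0.7 | 10% |
| 10% | 14.7% | 1.5 | 22% |

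**4. Effect on mean LOS (illustrative).** Assume 4 days for early exits and 100 days for the others. Historical mean LOS is lowered by e × (100 − 4): 2.9, 4.8 and 9.6 days at e = 3%, 5% and 10%.

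**5. Effect of refusal, if refusers are removed (illustrative).** With refusal rates h among hydrocephalus cases and n among the rest, the observed rate is 0.132(1 − h)/[0.132(1 − h) + 0.868(1 − n)].

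- h = 20%, n = 10%: 0.1056/0.8868 = 11.9%.
- h = 10%, n = 20%: 0.1188/0.8132 = 14.6%.
- h = n: 13.2%, unchanged.

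The sign depends on who refuses, which the documents do not tell us.

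**The case against.** The strongest reply is that little of this is established. Caregiver consent means that incapacity, the obvious barrier in this population, excludes nobody. Baseline assessment falls within 7 days of admission (2.4), and nothing suggests that consent is delayed. If it is taken at admission, the early-exit route nearly vanishes. All of this stands, and it limits the size of the problem.

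A reader might go further and infer that the cohorts are in fact selected on survival and outcome, because reachable historical survivors can leave by refusing while the dead all stay in. The documents do not support that. They do not say that refusers are removed, and they give no rates.

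The magnitudes can also be challenged. The inputs e, 4 days and 100 days are assumptions. The 13.2% comes from another sample: at 50–60 a year, 2015–2019 would hold 5 × 50 = 250 to 5 × 60 = 300 patients, not 621. That stands too, so the figures show scale only.

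It can be said that sections 2.1 and 2.3 do not conflict, since the waiver is what lets all patients be kept. That holds only if a refusal, once sought and given, has no effect; the text leaves this open.

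Finally, refusal counts are ordinary reporting, which a condensed article may leave to the full protocol. Agreed: their absence is not the point here. The unequal starting point is, because it follows from the entry rules that the article does state.

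**Conclusion.** The consent rules create a risk of differential selection, through patients who leave very early. The possible distortion runs in opposite senses: towards the new protocol for the detection rate, against it for LOS. Under the assumed 3–10% of early exits it is about 0.4–1.5 points of detection rate and, with the assumed stays, about 3–10 days of mean LOS. It would be close to zero if prospective consent is taken at admission or if early exits are rare, and the documents do not allow a choice between these cases.

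Selection through refusal is possible, but its existence and direction cannot be determined. The planned covariate adjustment does not address either route. The change is worth making because it is cheap; a material bias has not been shown.

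**What to change.** 1. In 2.1 and 2.5, define the between-cohort comparison in both cohorts as patients alive and still hospitalised at the end of the existing T0 window (day 7). Admission, discharge and death dates are enough to apply this.
2. Reconcile the word *all* in 2.1 with 2.3: state whether a historical patient who is reached and refuses is left out, and when prospective consent is taken.
3. Acknowledge selection by refusal as a limitation and give counts by cohort (eligible, refused, waived, lost before consent), logged during recruitment.

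**Cost.** Wording, a count table, and the loss of a few short-stay patients. With 275 historical and 110 prospective patients (midpoints of 250–300 and 100–120) and rates of 13.2% and 20%, the standard error of the difference is √(0.132 × 0.868/275 + 0.20 × 0.80/110) = 0.0433. Dropping 10% of the historical patients, all undiagnosed, gives √(0.1467 × 0.8533/247.5 + 0.20 × 0.80/110) = 0.0443, an interval about 2% wider.

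**Limits.** The day-7 start does nothing about refusal, and if consent comes after day 7, losses between day 7 and consent remain. Bounding refusers as all undetected or all detected would add little. If 50–70% are reachable and 10–30% of those refuse (assumed), refusers are 5–21% of the cohort, and 13.2% becomes 12.5–17.5% at the low end and 10.4–31.4% at the high end. The latter range spans the expected 20%. Consent arrangements and patient care are unchanged.

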### 2.4. Clinical Diagnostic Protocol and Study Assessments

A multidisciplinary team of physiatrists, neuroradiologists, neuropsychologists and neurosurgeons designed the new protocol for the diagnosis of suspected secondary hydrocephalus and its confirmation, based on the best recommendations in the literature [18,19,20]. The timing and procedures included in the diagnostic protocol are shown in Figure 1. 

Within 7 days (week 1) of hospital admission, i.e., at baseline (T0), patients with sABIs will undergo the following evaluations:Socio-demographic and anamnestic data collection;Neurological examination;Clinical and functional assessment;Neuroradiological exam (brain CT);Neurophysiological exams.

Clinical and functional assessments will be performed at weeks 3 and 5, before the multidisciplinary team meeting. An additional CT scan and a brain MRI will be performed after 30 days (week 5) from admission (T1) to assess the presence of ventricular dilation signs. The first multidisciplinary team meeting will be held about 40 days (week 6) after admission, with the aim of evaluating the results of the neurological examination, neuroradiological exams, and clinical and functional assessments. The multidisciplinary team will identify patients with suspected hydrocephalus based on the presence of at least one of the following criteria:Neuroradiological criteria: increase in ventricular dimensions with supratentorial and subtentorial ventricular dilation, or both; sulcal reduction at the convexity; Evan’s index increase; callosal thickness reduction; callosal angle increase; presence of periventricular white matter changes; presence of aqueductal flow void.Clinical criteria: worsening or stopping of clinical recovery as assessed based on clinical scales and functional tests.

Patients with “suspected hydrocephalus” will undergo further evaluations to confirm the diagnosis, specifically:High-volume tap test (TT);CSF examination;Clinical and functional assessments 1, 3 and 7 days after TT;Multidisciplinary team evaluation 7 days after TT.

Diagnosis confirmation derives mainly from the improvement of the patient’s clinical/neurological condition after CSF TT, measured as an improvement in the score of the clinical scales before and after the test or as an improvement in the performances in the functional tests. The main clinical rating scale is the Disability Rating Scale (DRS). The Levels of Cognitive Functioning (LCF) scale corroborates the DRS result. The Coma Recovery Scale Revised (CRS-R) will be used for patients with low responsiveness or severe disturbance of consciousness. 

Specifically, the diagnosis will be confirmed when at least one of the following changes occurs after TT:
Decrease in the DRS score;Increase in the LCF score;Increase in one of the CRS-R scale’s items that identify a minimally conscious state or emergence from a minimally conscious state;Improvement in one of the functional tests (TUG, 10 mWT, POMA).

Patients with a confirmed diagnosis will receive an indication of surgical treatment with shunt placement.

Both the severity of the clinical condition and the consent being denied by family are reasons that preclude the intervention, even in the case of a diagnosis confirmation.

During the hospital stay, the multidisciplinary team will evaluate the presence of suspected hydrocephalus in patients with no previous diagnosis. Patients with suspected hydrocephalus will be treated following the clinical diagnostic protocol just described.

The study flow is described in Figure 2. 

All patients will undergo a reassessment of all clinical and functional scales, neurological and neurophysiological examinations and a brain CT scan at three time points: 1 month after surgery for those treated with a VPS/VAS or at 3 months from hospital admission for patients without a diagnosis of hydrocephalus or who did not receive a VPS/VAS placement (T2); at discharge (T3); and 1 year after hospitalization (T4). All the patients will undergo a brain MRI at T3 and, if prescribed by the multidisciplinary team, at T4. 

Table 1 summarizes the clinical parameters, clinical measurement scales, functional tests, and neurophysiological and neuroradiological exams included in the study.

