## 5. Conclusions

We designed a novel clinical diagnostic protocol to improve the accuracy of secondary hydrocephalus diagnosis in patients with sABIs. We expect that it will result in a more appropriate assessment and timely treatment of patients, with the ultimate goal of improving their prognosis.

Should this clinical diagnostic protocol prove to be useful, it could be adopted by other rehabilitation centers to improve hydrocephalus diagnosis and treatment, thereby reducing the length of hospital stay and accelerating recovery with benefits for both patients and hospitals. 

In addition, this protocol may inform future diagnostic and prognostic guidelines for the inclusion of the tap test, timely and standardized neuroimaging and an early approach of the multidisciplinary team in the standard of secondary hydrocephalus diagnosis in patients with sABIs. 

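### Hydrocephalus cases are ascertained differently in the two cohorts, so a higher detection rate cannot be read as better or more accurate detection

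*Protocol article*

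**What the plan says.** In the prospective cohort (section 2.4) every patient is assessed and imaged on a fixed schedule, and one listed radiological or clinical criterion is enough for suspicion. Suspected patients have a tap test, then "Clinical and functional assessments 1, 3 and 7 days after TT" and a team evaluation on day 7. After that, "the diagnosis will be confirmed when at least one of the following changes occurs after TT": a lower DRS, a higher LCF, a gain in a CRS-R item that marks a minimally conscious state or emergence from it, or a better TUG, 10 mWT or POMA. No size of change is given, and the rule does not say which day counts. Confirmation leads to an indication for a shunt.

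The control group (section 2.1) is all sABI inpatients from 2015 to 2019. The article does not say how their hydrocephalus was diagnosed. Of a previous series of 621 patients, with 13.2% incidence, the Introduction says: "The diagnosis was based on the previously indicated combination of clinical and radiological criteria".

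Detection rate is the first aim and the first between-cohort comparison in section 2.5. One aim is limited to diagnosed patients: "To reduce the overall length of hospitalization (LOS) and the occurrence of complications in patients diagnosed with and treated for hydrocephalus". Section 3 expects better discharge outcomes among patients with hydrocephalus, and expects them to do about as well as patients without it. The Abstract says that no gold standard exists. The Discussion nevertheless speaks of validating the protocol, and the Conclusions say: "We designed a novel clinical diagnostic protocol to improve the accuracy of secondary hydrocephalus diagnosis in patients with sABIs".

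**The concern.** The detection rate depends on the rule and the intensity of case finding as well as on the disease. In the prospective cohort both are set by the new protocol; in the historical cohort they were whatever practice was at the time. An any-one-of rule without a minimum change, read on up to three days, will confirm some patients through measurement variation or spontaneous recovery. Each such patient raises the detection rate, and the plan has no independent standard that would count that patient as an error. Over-diagnosis would therefore look like success on the first aim, although a confirmed diagnosis carries an indication for surgery.

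The regression adjustment in section 2.5 deals with patient characteristics. It cannot correct an outcome that is ascertained differently in the two groups. The limitations in the Discussion do not mention the problem.

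There is a second consequence. If the added cases are milder than true cases, the average outcome of diagnosed patients improves without any patient doing better, and the gap between diagnosed and undiagnosed patients narrows.

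**Working it through.** **Inputs from the documents.** "The expected annual flow of patients with sABIs is 50–60" (section 2.2); two years of recruitment; about 20% expected with hydrocephalus; 13.2% of 621 in the previous series (Introduction); "Two-sided tests will be carried out" and "the statistical significance level will be set at 0.05" (section 2.5).

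**Assumptions, not in the documents.** True prevalence *p* = 13.2% in both cohorts, with all true cases found in both; *s*, the share of non-cases suspected and tapped; *f*, the share of those falsely confirmed; *q*, the chance of improvement per measure per day; the outcome gap between true cases and non-cases; and historical size 250–300 (5 years × 50–60).

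**1. The plan's own figures.** 2 × 50 = 100 and 2 × 60 = 120 patients; 20% of these is 20 to 24 cases. This agrees with section 2.2.

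**2. False confirmation needed to reach 20% with no extra true case.** Apparent rate = *p* + (1 − *p*) × *s* × *f*. Setting this to 0.20 gives *s* × *f* = (0.20 − 0.132)/(1 − 0.132) = 0.068/0.868 = 0.078. In patients this is 0.068 × 100 = 6.8 to 0.068 × 120 = 8.2. The false share of the diagnosed is 0.068/0.20 = 34%.

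**3. How large *f* might be.** For *k* applicable measures and *L* days, independent readings give *f* = 1 − (1 − *q*)^(*kL*). Taking *k* = 2 (DRS and LCF only) to 5 (adding the three functional tests) and *q* = 0.05:
- one day: 1 − 0.95^2 = 10% to 1 − 0.95^5 = 23%;
- three days: 1 − 0.95^6 = 27% to 1 − 0.95^15 = 54%;
- with correlated readings (0.5 between measures, 0.8 between days, simulated): 9–17% for one day and 16–27% for three.

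Over *q* = 0.02 to 0.10, the correlated three-day range is 7–43%. At *q* = 0.05 (unrounded *f* 15.5% to 26.6%), step 2 would need *s* between 0.078/0.266 = 29% and 0.078/0.155 = 51% of non-cases tapped.

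**4. Apparent detection rate with no true gain** (275 historical against 110 prospective):

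| *s* | *f* | Apparent rate | Chance of a significant result |
|---|---|---|---|
| 0.2 | 0.2 | 16.7% | 15% |
| 0.3 | 0.2 | 18.4% | 27% |
| 0.3 | 0.3 | 21.0% | 48% |
| 0.5 | 0.3 | 26.2% | 85% |

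A rise from 13.2% to exactly 20% would be significant in about 37–42% of studies (100–120 against 250–300).

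**5. Shift in diagnosed patients.** Shift = false share × outcome gap. If non-cases do 2 to 4 DRS points better, 0.34 × 2 = 0.7 and 0.34 × 4 = 1.4 points. If the false positives resemble the other non-cases, the diagnosed-versus-undiagnosed gap shrinks by the same 34%. The whole-cohort mean does not move, because relabelling changes nobody's score.

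**The case against.** The strongest reply is that a changed case definition is not documented. The previous series is not said to be the control cohort, and the Introduction already lists improvement after high-volume lumbar puncture among the usual criteria, also without a threshold. Making tap response the main route could even narrow the definition in some respects. This stands: a reader might infer that the new rule is looser, but the documents show only that ascertainment differs and that the historical definition is not given.

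The rule is also not open to any scale in Table 1. Only the listed measures count, CRS-R is for patients with low responsiveness, suspicion comes first, and the team evaluates on day 7. Patients suspected on clinical grounds have worsened or stopped recovering, so spontaneous recovery is a concern mainly for those suspected on imaging alone. This stands too and limits how large *f* is likely to be.

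A reader might further infer that the planned LOS, complication and discharge comparisons are biased by relabelling. As worded, section 2.5 compares the cohorts without restricting to diagnosed patients, so they are not, and harm from over-diagnosis could still show there.

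Finally, more intensive case finding is the intervention, and the lack of a gold standard is openly stated. A higher yield is therefore a fair descriptive result. That does not support calling it accuracy or validation.

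**Conclusion.** The point holds for the detection rate and for conclusions drawn within diagnosed patients. The rate mixes real detection with a difference in ascertainment, and nothing in the stated analysis separates them. About 7.8% false confirmation among non-cases, some seven or eight patients over two years, would account for the whole expected rise from 13.2% to 20%. This rests on equal true prevalence and full sensitivity in both cohorts. If historical cases were missed, as the authors suspect, part of any rise would be real. The false-confirmation rate is unknown, so a spurious increase could appear; it is neither certain nor certain to be significant.

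Claims about diagnosed patients, and the planned diagnosed-versus-undiagnosed comparison with its expectation of comparable outcomes, could shift through case mix alone. Whole-cohort comparisons are unaffected by relabelling.

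Section 2.4 also contradicts itself: LCF is described as supporting the DRS result, yet an LCF increase alone is listed as sufficient. These statements must be reconciled. Severity: should be fixed.

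**What to change.** Leave clinical management, including the confirmation rule, to the investigators and change the analysis and the claims.

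1. Call the detection rate *diagnostic yield*, drop the accuracy and validation conclusions, and add the difference in ascertainment to the limitations in the Discussion.
2. Report next to it the proportion shunted and the proportion shunted with later improvement, defined identically in both cohorts where records allow. Say that these also depend on the confirmation rule and on spontaneous recovery.
3. State that LOS, complication and discharge-outcome conclusions rest on all eligible patients in each cohort. Make diagnosed-only and diagnosed-versus-undiagnosed results descriptive.
4. Report confirmations by component and by day, and reconcile the two statements on LCF.

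Applying the improvement rule to the change from week 3 to week 5, before any tap test, could give an exploratory background rate only. The interval and number of looks differ, and clinically suspected patients are partly selected for not improving over it.

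The cost is wording, some chart abstraction from historical records that the Discussion warns may be incomplete, diluted whole-cohort effects and a more modest headline. The prospective assessments are already planned.
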